##### 2.7.2.2. Cost-effectiveness analysis

The VAS score will be measured 4 weeks after discharge to determine the reduction in the VAS score in each CP applied and non-applied group, and the medical expense in each group until 4 weeks after discharge will be calculated. A cost-effectiveness analysis will be performed by calculating the ICER based on the difference in costs between the groups and the reduction in the VAS score.

#### 2.7.3. Safety evaluation

##### 2.7.3.1. Adverse events

Adverse events will be determined based on the severity and causal relationship with the test drug, and the incidence rate of adverse events, incidence rate of adverse events that caused dropout, and expression rate of serious adverse events will be analyzed.

##### 2.7.3.2. Clinical pathological examinations (hematologic/hematochemical test)

The difference in the pathological findings at the time of hospitalization and discharge will be tested using a paired *t* test for continuous variables, and the differences between the groups will be evaluated using a *t* test.

##### 2.7.3.3. Vital signs (blood pressure, pulse, respiratory rate, and body temperature)

The vital signs will be evaluated 3 times a day at 8-hour intervals from admission.

### 2.8. Statistical analysis

#### 2.8.1. Efficacy evaluation analysis

##### 2.8.1.1. Primary outcome analysis

The primary outcomes will be analyzed based on the treatment groups. For each group, a normal distribution will be assumed for the difference in the VAS score measured on day 1 of hospitalization and at 4 weeks after discharge, and a *t* test will be performed. The means between the treatment groups (CP and control groups) will be compared. If normality is confirmed through the normality test for the VAS scores, the Mann–Whitney test will be performed.

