## 2. Materials and methods

### 2.1. Study design

This single-center prospective observational study will be performed at Kyung Hee University Medicine Hospital and Kyung Hee University Korean Medicine Hospital to analyze the effectiveness, economy, and safety of using an integrated medical service CP in patients with L-HNP. The patients will be divided into groups that apply critical pathway of integrative medical services and those who do not.

From among the patients who agree to participate in the study, those who meet the inclusion criteria will be registered as research subjects. Among them, those who agree to participate in the integrated medical service CP will be assigned to the test group (integrated medical service CP applied group) and those who do not will be assigned to the control group (integrated medical service CP non-applied group). Both groups are further divided into a conservative treatment (CONS) group, an open discectomy (DISCEC) group, and an interbody fusion (FUSION) group based on the main medical treatment. In the test group, inpatient treatment will be administered according to the pathway of the prescribed protocol. In the control group, inpatient treatment will be administered based on the treating doctor’s judgment, without a prescribed pathway. The test group patients will be discharged after being hospitalized for a set hospitalization date, whereas in the control group, the time of discharge will be determined according to the judgment of the clinician. The study will be completed when the patients are evaluated during an outpatient visit to the Department of Neurosurgery of Kyung Hee Medical Center 4 weeks after discharge.

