### 2.4. Clinical trial plan and critical pathway schedule

Among patients with lumbar intervertebral disc herniation visiting the Neurosurgery outpatient department of Kyung Hee Medical Center, patients with a VAS score of 7 or higher who require hospitalization can consent to participate in this study. Following patient consent, the doctors and research nurses will screen the patients according to the inclusion and exclusion criteria, enroll those who pass the screening, and confirm the participants intention to receive treatment using an integrated medical service CP. Depending on their intention to participate in the CP application, participants will be classified into the test or control group. Upon admission, the patients will be assigned to the CONS group, DISCEC group, and FUSION groups according to the judgment of the medical staff. The test group will receive inpatient treatment according to a previously developed integrated medical service CP plan, and the control group will receive inpatient treatment according to the clinician’s judgment without a set protocol. The study will be deemed complete when all patients will be evaluated during an outpatient visit to the Neurosurgery Department of Kyung Hee Medical Center 4 weeks after discharge.

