### 2.7. Outcomes

#### 2.7.1. Efficacy evaluation

##### 2.7.1.1. Primary outcome

Considering the CONS, DISCEC, and FUSION groups, we will evaluate whether the decrease in the VAS score in the CP group is statistically significant compared to that in the corresponding control group on day 1 of hospitalization and 4 weeks after discharge.

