##### 2.8.1.2. Secondary outcome analysis

The differences in VAS scores measured on day 1 of hospitalization and at 4 weeks after discharge in each treatment group will be analyzed with a linear model assuming a normal distribution. In the analysis model, including the treatment group (CP and control groups), age, sex, type of insurance related to back pain, region of residence, Charlson Comorbidity Index (CCI), surgery status, and hospitalization record as covariates and factors, we will evaluate if the VAS score reduction in the CP group is statistically significant compared to that in the control group. If the normality of the VAS scores is not satisfied, we will use a sandwich estimator or perform a nonparametric statistical analysis.The differences in VAS scores measured on the day of hospitalization and discharge in each treatment group will be analyzed with a linear model assuming a normal distribution. In the analysis model, including the treatment group (CP and control groups), age, sex, type of insurance related to back pain, region of residence, CCI, surgery status, and hospitalization record as covariates and factors, we will evaluate if the VAS score reduction in the CP group is statistically significant compared to that in the control group. If normality of the VAS scores is not satisfied, we will use a sandwich estimator or perform a nonparametric statistical analysis.The differences in ODI, SF-36, and EQ-5D-3L scores measured on day 1 of hospitalization and 4 weeks after discharge in each treatment group will be analyzed with a linear model assuming a normal distribution. In the analysis model, including the treatment group (CP and control groups), age, sex, type of insurance related to back pain, region of residence, CCI, surgery status, and hospitalization record as covariates and factors, we will evaluate if the VAS score reduction in the CP group is statistically significant compared to that in the control group. If normality of the ODI, SF-36, and EQ-5D-3L scores is not satisfied, we will use a sandwich estimator or perform a nonparametric statistical analysis.The differences in ODI, SF-36, and EQ-5D-3L scores measured on the day of hospitalization and discharge in each treatment group will be analyzed with a linear model assuming a normal distribution. In the analysis model, including the treatment group (CP and control groups), age, sex, type of insurance related to back pain, region of residence, CCI, surgery status, and hospitalization record as covariates and factors, we will evaluate if the VAS score reduction in the CP group is statistically significant compared to that in the control group. If normality of the ODI, SF-36, and EQ-5D-3L scores is not satisfied, we will use a sandwich estimator or perform a nonparametric statistical analysis.The average length of hospital stay in the CP group and control group will be compared by a 2-sample *t* test. If normality is not satisfied, the Wilcoxon rank-sum test will be performed.After patient discharge, we will perform the χ^2^ test or Fisher exact test for the test and control groups (CP applied and CP non-applied group) for staff satisfaction data obtained through a questionnaire.After patient discharge, we will perform a homogeneity test for the test and control groups (CP applied and CP non-applied groups) to evaluate patient satisfaction using the data obtained from the questionnaires.The consultation waiting time will be compared between the CP and control groups was compared using a 2-sample *t* test. If normality is not satisfied, the Wilcoxon rank-sum test will be performed.To compare the additional amount of pro re nate analgesic consumed between the CP and control groups, a 2-sample *t* test will be used. If normality is not satisfied in the normality test for additional analgesic use, the Wilcoxon rank-sum test will be performed.We will perform ANOVA (analysis of variance) to compare the average CP application and completion rates in the CONS, DISCEC, and FUSION groups of the CP group.

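### Patients choose their own study group, yet the primary test is an unadjusted t test and the covariate-adjusted model of the same endpoint is only secondary, which leaves the primary result exposed to confounding

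*Protocol article*

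**What the plan says.** Section 2.1 describes a single-center prospective observational study and forms the groups by consent to the pathway: "those who agree to participate in the integrated medical service CP will be assigned to the test group". Patients who do not agree become controls. Section 2.4 repeats the rule: "Depending on their intention to participate in the CP application, participants will be classified into the test or control group". On admission, after that choice, "the patients will be assigned to the CONS group, DISCEC group, and FUSION groups according to the judgment of the medical staff". The article names no randomization, matching, weighting or propensity score.

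Section 2.7.1.1 sets the primary question separately for conservative treatment, discectomy and fusion: "we will evaluate whether the decrease in the VAS score in the CP group is statistically significant compared to that in the corresponding control group". Section 2.8.1.1 answers it with a t test on the change from day 1 to 4 weeks after discharge ("a normal distribution will be assumed for the difference in the VAS score measured on day 1 of hospitalization and at 4 weeks after discharge"). It adds: "The means between the treatment groups (CP and control groups) will be compared". The alternative test named there, Mann–Whitney, is unadjusted too.

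Section 2.8.1.2 takes the same VAS change over the same interval, which "in each treatment group will be analyzed with a linear model assuming a normal distribution". That model includes age, sex, insurance type, region, Charlson index, surgery status and hospitalization record. Day-1 VAS is not in the list. The model stands under the secondary analyses.

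**The concern.** A two-sample t test attributes any systematic difference in means to the CP. That is safe when the groups are exchangeable, and randomization would secure this. Here the patient's own decision forms the groups, so those who accept and those who decline may differ in pain, expectation, comorbidity or earlier admissions. Any such factor that also affects recovery enters the primary estimate and its p-value.

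The study sets out to compare the effectiveness of the CP, and the primary test is the result most readers will take from it. Enrolling more patients does not help, because bias does not shrink with sample size. Analysis within the three strata deals only with the main treatment received, and staff assign that after the CP choice has been made.

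This is a choice the protocol states, not a detail left to a later document. An analysis plan could add sensitivity analyses, but making another analysis primary would contradict section 2.8.1.1.

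**Working it through.** **Inputs from section 2.5.** Planned difference 1.15 VAS points; two-sided 5% level; 80% power; pre–post correlation 0.5. SDs before and after treatment are 1.29 and 0.84 (treatment arm of the cited study) and 1.21 and 0.93 (control arm).

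**The plan's own figure.** The SDs of change are √(1.29² + 0.84² − 1.29×0.84) = 1.13 and √(1.21² + 0.93² − 1.21×0.93) = 1.10, which pool to 1.12. Then n = 2×1.12²×(0.842 + 1.960)² / 1.15² = 14.9, so 15 per group. With 10% dropout this is 15/0.9 = 16.7, so 17 per group and 6×17 = 102 in total. The stated numbers reproduce. The formula takes the CP effect as the only expected difference between the groups.

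**Illustration 1: selection bias acting directly on the change.** The true CP effect is set to zero, with n = 15 per group and SD 1.12. For a bias b, the t statistic has 28 degrees of freedom and noncentrality b / (1.12×√(2/15)); the critical value is 2.048. The bias is assumed, since the protocol gives none.

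| Assumed bias in mean change (points) | False-positive rate of each primary t test |
|---|---|
| 0 | 5.0% |
| 0.25 | 9.1% |
| 0.5 | 21.9% |
| 0.75 | 42.5% |
| 1.0 | 65.6% |

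A bias of 0.5 is under half the planned effect (0.5/1.15 = 43%). At 17 per group its rate is 24.3%, slightly higher than at 15.

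**Illustration 2: a gap in day-1 VAS.** Suppose both groups regress toward a common mean. The slope of follow-up on baseline is ρ×SD(after)/SD(before):

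- 0.5×0.84/1.29 = 0.326
- 0.5×0.93/1.21 = 0.384

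A baseline gap g shifts the difference in change by (1 − slope)×g.

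- g = 0.5: shift 0.31 to 0.34, false-positive rate 11–13%.
- g = 1.0: shift 0.62 to 0.67, false-positive rate 31–36%.

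**How far illustration 2 depends on its model.** I simulated a stable 0.5-point gap, present at both times, with no CP effect, 15 per group, SDs 1.25 and 0.88 (midway between the two arms) and correlation 0.5. The t test on change rejected in about 5% of runs, and a model adjusted for baseline in about 19%. With the same SDs and regression to a common mean, the order reversed: about 12% for the t test on change and about 5% for the adjusted model. The protocol does not say which situation applies.

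**The case against.** The strongest reply is that the study is openly observational and already prespecifies an adjusted analysis of the same endpoint at the same time point. Both results will be available, so the dispute is about ranking. That is fair as far as it goes, but the ranking decides which result carries the study's claim, and the plan gives that place to the analysis with less protection.

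A second reply is that baseline adjustment is not automatically right for self-selected groups. This stands. If the groups differ stably, the change score is unbiased on that account and adjusting for day-1 VAS introduces bias, as the simulation shows. It limits the 11–13% and 31–36% figures to the common-mean model and is a reason to keep the t test on change in the report. It does not rescue the unadjusted test from the other possible differences between the groups.

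A reader might go further than the documents allow in three ways:

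- That the primary result *is* confounded, in a known direction. The protocol gives no data on how acceptors and decliners differ; it shows exposure only.
- That the entry rule of VAS 7 or higher makes the baseline problem worse. The rule applies to both groups, so regression common to both cancels in the comparison, and nothing in the protocol shows an aggravation.
- That exchanging the two planned analyses would settle the matter. The secondary model omits day-1 VAS. Its seven covariates besides the CP term are many for 30 to 34 patients per stratum (2×15 to 2×17). No listed covariate measures preference or expectation.

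**Conclusion.** The point holds as exposure to confounding of unknown direction and size. The groups form by patient choice, the primary test is unadjusted, and an adjusted model of the same endpoint ranks below it. All three facts are on the face of the protocol.

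The sizes are illustrations. About 22% instead of 5% rests on an assumed 0.5-point bias in mean change, SD 1.12, 15 per group and no true effect. The 11–13% rests on an assumed 0.5-point baseline gap and, in addition, on both groups regressing to a common mean with the protocol's SDs and correlation. The sample size arithmetic is not in dispute.

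**What to change.** - Make a covariate-adjusted linear model the primary analysis. Build on the model in section 2.8.1.2, add day-1 VAS, and shorten the covariate list, for example to age, sex, Charlson index and hospitalization record.
- Keep one CP-versus-control estimate for each of conservative treatment, discectomy and fusion, as section 2.7.1.1 asks. Either fit the model within each stratum, or fit all patients together with a CP-by-stratum term. One pooled effect would change the primary question.
- Report the t test on change as an unadjusted supportive result. Setting it beside the adjusted estimate also shows how much depends on the baseline-adjustment assumption.
- Word the conclusion as an adjusted association.

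**Cost.** No new data are needed: day-1 VAS and the covariates are already planned. The change does more than reorder analyses, because it modifies the planned model. The primary result becomes model-dependent, and unmeasured confounding such as by expectation or preference remains. The protocol gives no covariate R² and no expected imbalance, so a revised sample size cannot be derived from it.

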##### 2.8.1.2. Secondary outcome analysis

The differences in VAS scores measured on day 1 of hospitalization and at 4 weeks after discharge in each treatment group will be analyzed with a linear model assuming a normal distribution. In the analysis model, including the treatment group (CP and control groups), age, sex, type of insurance related to back pain, region of residence, Charlson Comorbidity Index (CCI), surgery status, and hospitalization record as covariates and factors, we will evaluate if the VAS score reduction in the CP group is statistically significant compared to that in the control group. If the normality of the VAS scores is not satisfied, we will use a sandwich estimator or perform a nonparametric statistical analysis.The differences in VAS scores measured on the day of hospitalization and discharge in each treatment group will be analyzed with a linear model assuming a normal distribution. In the analysis model, including the treatment group (CP and control groups), age, sex, type of insurance related to back pain, region of residence, CCI, surgery status, and hospitalization record as covariates and factors, we will evaluate if the VAS score reduction in the CP group is statistically significant compared to that in the control group. If normality of the VAS scores is not satisfied, we will use a sandwich estimator or perform a nonparametric statistical analysis.The differences in ODI, SF-36, and EQ-5D-3L scores measured on day 1 of hospitalization and 4 weeks after discharge in each treatment group will be analyzed with a linear model assuming a normal distribution. In the analysis model, including the treatment group (CP and control groups), age, sex, type of insurance related to back pain, region of residence, CCI, surgery status, and hospitalization record as covariates and factors, we will evaluate if the VAS score reduction in the CP group is statistically significant compared to that in the control group. If normality of the ODI, SF-36, and EQ-5D-3L scores is not satisfied, we will use a sandwich estimator or perform a nonparametric statistical analysis.The differences in ODI, SF-36, and EQ-5D-3L scores measured on the day of hospitalization and discharge in each treatment group will be analyzed with a linear model assuming a normal distribution. In the analysis model, including the treatment group (CP and control groups), age, sex, type of insurance related to back pain, region of residence, CCI, surgery status, and hospitalization record as covariates and factors, we will evaluate if the VAS score reduction in the CP group is statistically significant compared to that in the control group. If normality of the ODI, SF-36, and EQ-5D-3L scores is not satisfied, we will use a sandwich estimator or perform a nonparametric statistical analysis.The average length of hospital stay in the CP group and control group will be compared by a 2-sample *t* test. If normality is not satisfied, the Wilcoxon rank-sum test will be performed.After patient discharge, we will perform the χ^2^ test or Fisher exact test for the test and control groups (CP applied and CP non-applied group) for staff satisfaction data obtained through a questionnaire.After patient discharge, we will perform a homogeneity test for the test and control groups (CP applied and CP non-applied groups) to evaluate patient satisfaction using the data obtained from the questionnaires.The consultation waiting time will be compared between the CP and control groups was compared using a 2-sample *t* test. If normality is not satisfied, the Wilcoxon rank-sum test will be performed.To compare the additional amount of pro re nate analgesic consumed between the CP and control groups, a 2-sample *t* test will be used. If normality is not satisfied in the normality test for additional analgesic use, the Wilcoxon rank-sum test will be performed.We will perform ANOVA (analysis of variance) to compare the average CP application and completion rates in the CONS, DISCEC, and FUSION groups of the CP group.

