#### 2.3.2. Exclusion criteria

(1).Suspected malignant tumor, spinal infection, or osteoporotic compression fracture.(2).Need of immediate surgery due to another disease.(3).Serious underlying disease.(4).More pain due to musculoskeletal disease than due to L-HNP.(5).Medical benefits, Auto insurance.(6).Other patients whom the investigator deems unsuitable to apply CP in this clinical trial.

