#### 2.5.1. Average change in the VAS score

The average change in VAS was calculated as 2.27 to 6.14 = −3.87 in the treatment group and 3.37 to 6.09 = −2.72 in the control group. Therefore, the difference in the change in the VAS score before and after treatment between the 2 groups was d=−3.87 to (−2.72) = −1.15.

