#### 2.5.2. Variance in the change in the VAS score

Assuming that the correlation coefficient (ρ) for pre- and posttreatment was 0.5, the variance in the VAS score change before and after treatment for the treatment and control groups was calculated as follows:

Treatment group: Var(A−B)=Var(A)+Var(B)−2ρSD(A)SD(B)$=1.29^{2}+0.84^{2}-2*0.5*1.29*0.84\approx 1.13^{2}$

Control group: Var(A−B)=Var(A)+Var(B)−2ρSD(A)SD(B)$=1.21^{2}+0.93^{2}-2*0.5*1.21*0.93\approx 1.10^{2}$

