#### 2.5.3. Pooled variance calculation

The pooled variance was calculated to determine the number of subjects, assuming that the variance of the VAS score change before and after treatment in the treatment and control groups was the same.

$$\begin{array}{l} \sigma^{2}=\frac{\left(45-1\right)\times 1.13^{2}+\left(37-1\right)\times 1.10^{2}}{46+37-2}\approx 1.12^{2} \end{array}$$

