#### 2.5.4. Calculation of the number of subjects

Assuming that the significance level (α) is 5% and the test power (1-β) is 80%, the number of subjects in each group is calculated so that the ratio of the 2 groups is 1:1.

$$\begin{array}{l} n=\frac{2\sigma^{2}{\left(Z_{1-\beta }+Z_{1-\frac{\alpha }{2}}\right)}^{2}}{d^{2}}=\frac{2\times 1.12^{2}{\left(Z_{0.8}+Z_{0.975}\right)}^{2}}{{\left(-1.15\right)}^{2}}\approx 15 \end{array}$$

The CP group is divided into the CONS, DISCEC, and FUSION groups, and CP non-applied group is also divided into the corresponding 3 groups. The minimum number of subjects required for this study is 15 per group, with a total of 90; however, considering the dropout rate (10%), a total of 102 subjects (17 per group) will be enrolled.

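### The adjusted models analyse change scores without the outcome's own day-1 value, which costs precision and over-corrects any day-1 difference between the self-selected groups

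*Protocol article*

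**What the plan says.** Section 2.8.1.2 describes four linear models, each fitted within a treatment stratum (CONS, DISCEC, FUSION). Two concern VAS (to 4 weeks after discharge, and to discharge). Two concern the other scales at the same time points, the first of them introduced as "The differences in ODI, SF-36, and EQ-5D-3L scores measured on day 1 of hospitalization and 4 weeks after discharge in each treatment group". The outcome is a difference from the start of hospitalization in every case. All four models carry the same adjustment list beside the CP indicator: "age, sex, type of insurance related to back pain, region of residence, Charlson Comorbidity Index (CCI), surgery status, and hospitalization record as covariates". None lists the day-1 value of VAS, ODI, SF-36 or EQ-5D-3L. Both models for ODI, SF-36 and EQ-5D-3L then state that the reduction in VAS is what will be tested.

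The primary analysis (section 2.8.1.1) is an unadjusted t test on VAS change. Groups are formed by whether the patient agrees to the CP (sections 2.1, 2.3 and 2.4), so there is no randomisation. The sample size in section 2.5 also rests on VAS change, with the step "Assuming that the correlation coefficient (ρ) for pre- and posttreatment was 0.5".

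**The concern.** The models in section 2.8.1.2 are the only covariate-adjusted comparisons in the article. Because patients choose their group, adjustment matters more here than in a randomised trial, and pain on admission may plausibly differ between those who accept the pathway and those who decline it. The day-1 value is already measured for every scale, yet it enters only by subtraction. Subtraction is right on average only if a patient one point worse on day 1 is also expected to be one point worse at follow-up. If the true slope is well below 1, the change score carries avoidable noise, and a day-1 difference between groups is corrected by too much.

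Two smaller matters sit in the same text. Surgery status is not defined; if it means the index operation it is constant within each stratum and cannot be estimated. And the sentence on the tested effect in the ODI, SF-36 and EQ-5D-3L models names the wrong outcome.

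**Working it through.** **Inputs (sections 2.5 to 2.5.4).** Before and after SDs: treatment 1.29 and 0.84 (n = 45), control 1.21 and 0.93 (n = 37). Correlation 0.5. Difference in change 1.15. Two-sided 5%, 80% power, and "the ratio of the 2 groups is 1:1".

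**1. The plan's own figure.**
- Change SD, treatment: √(1.29² + 0.84² − 2·0.5·1.29·0.84) = 1.134. Control: √(1.21² + 0.93² − 2·0.5·1.21·0.93) = 1.097. Pooled on 44 and 36 df: 1.118, printed as 1.12.
- n = 2·1.12²·(0.842 + 1.960)²/1.15² = 14.89, so 15 per group. 15/0.9 = 16.7, so 17 per group, and 6 × 17 = 102.

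The stated sample size reproduces and is not in question.

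**2. Implied baseline slope.** Pooled within-group quantities:
- Var(B) = (44·1.29² + 36·1.21²)/80 = 1.574
- Var(A) = (44·0.84² + 36·0.93²)/80 = 0.777 (SD 0.88)
- Cov = 0.5·(44·1.29·0.84 + 36·1.21·0.93)/80 = 0.551
- Slope = 0.551/1.574 = 0.35

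A change score uses a slope of 1. With a day-1 difference of D points between the groups, the change-score and baseline-adjusted estimates differ by (1 − 0.35)·D = 0.65·D. For D = 1 that is 0.65/1.15 = 57% of the design effect. Over correlations from 0.7 to 0.3 the share runs from 44% to 69%.

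**3. Precision on the protocol's inputs.**
- Residual variance with day-1 VAS: 0.777 − 0.551²/1.574 = 0.584, SD 0.764.
- Variance of change: 1.574 + 0.777 − 2·0.551 = 1.249, SD 1.118.
- Ratio 0.584/1.249 = 0.47, a cut of about 53%. Over correlations from 0.3 to 0.7 the ratio is 0.42 to 0.49.
- Power at 15 per arm for 1.15: about 77.5% for a t test on change (SD 1.12), and 97.8% with day-1 VAS as the one covariate (27 df).

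**4. Allowing for the entry criterion.** The baseline means in Table 1 are 6.14 and 6.09, while section 2.3.1 requires VAS 7 or higher at one site. Assume that the Table 1 normal distributions are truncated to 7–10, with slope and residual unchanged. With each group's own slope (0.5·SD(A)/SD(B)), change variance = residual variance + (1 − slope)²·Var(B).

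| | Treatment | Control |
|---|---|---|
| Baseline SD after truncation | 0.61 | 0.57 |
| Slope | 0.326 | 0.384 |
| Residual SD | 0.727 | 0.805 |
| Change SD | 0.835 | 0.877 |
| Variance cut | 24% | 16% |

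Pooled change SD is 0.854 against a residual SD of 0.764. Power at 15 per arm is 94.5% against 97.8%.

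If the baseline SD is instead simply taken as 0.6 to 1.0 with the pooled slope of 0.35, the variance ratio is 0.79 to 0.58, a cut of about 21% to 42%.

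**5. Limits.** The power figures compare two simple models without the other seven covariates and with groups balanced on day 1. They are not the power of the models in section 2.8.1.2. The article gives no SDs or correlations for ODI, SF-36 or EQ-5D-3L, so nothing can be computed for them.

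**The case against.** The strongest reply is that the day-1 value is not ignored: it is subtracted. A reader might infer from the covariate list that baseline imbalance is left uncorrected. That is not so. On the protocol's inputs it is corrected by too much, with a slope of 1 in place of about 0.35. Nor does adding the covariate settle confounding. Without randomisation, change-score and baseline-adjusted models rest on different assumptions, and neither is automatically unbiased. Both points stand.

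The gain is also easily overstated. The rise from 77.5% to 97.8% uses Table 1 baselines that do not match the entry criterion, and 77.5% is the power of the unadjusted primary test, not of the adjusted models. Under truncation the change score itself becomes less noisy and the power gain is about 3 points. Truncation is uncertain too, because the criterion applies to either pain site. All of this stands. It reduces the size of the gain but does not remove it.

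A reader might also infer that the listed covariates hardly vary within a stratum. The document does not support that. At most two of the seven are candidates. Surgery status is undefined and could mean previous surgery. Section 2.3.2 excludes "Medical benefits, Auto insurance", but the article does not list the insurance types that remain.

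Finally, fitting one model to all patients with stratum as a factor would replace the stratum-specific comparisons set out in section 2.7.1 with a single common effect. That is a different question, and this point does not call for it.

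These are secondary models, and the primary test and sample size use change scores consistently. That limits the weight of the point. It does not make the omission sound, because the article writes out the covariate list in full four times.

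**Conclusion.** The point holds for what the article states: four change-score models with a fixed covariate list that omits the outcome's own day-1 value. For VAS, with the protocol's correlation of 0.5, the forced slope of 1 compares with an implied 0.35. A day-1 difference is therefore over-corrected by about 0.65 VAS points per point, relative to the baseline-adjusted estimate.

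Day-1 VAS alone removes about 53% of the variance of a raw change score on Table 1 inputs, and about 16–24% if entry truncates baseline to 7–10. In the truncated case the power gain at 15 per arm is small, from about 94% to 98%. These figures rest on the assumed correlation, a common linear slope and, for the lower range, the truncation assumption. For ODI, SF-36 and EQ-5D-3L the same reasoning applies, but its size is unknown.

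The VAS wording in the two models for the other scales is a plain textual error. Surgery status needs a definition.

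**What to change.** Keep the models within each treatment stratum and make three changes in section 2.8.1.2:

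1. Add the day-1 value of the analysed scale as a covariate to each of the four models.
2. Define surgery status, and drop any covariate that is constant within a stratum. This applies to surgery status if it means the index operation.
3. In the two models for ODI, SF-36 and EQ-5D-3L, replace the VAS reduction with the change in the named scale as the tested effect.

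Retain the unadjusted change comparison next to the baseline-adjusted one, and state that the two rest on different assumptions in a non-randomised comparison.

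The cost is a change of wording and one extra degree of freedom per model. No new data are needed, since the day-1 values are already collected, and the sample size is unaffected.
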